#### Hypothesis 2: non-inferiority of BPT to CBT

The second hypothesis will be tested by conducting a non-inferiority analysis with both measurements for depression, the PHQ-9, and the MADRS. The reason for this is that a predefined equivalence margin for the PHQ-9 already exists in literature, but this is not the case for the MADRS. For the PHQ-9, we will use the established equivalence margin of 1.9 points [36, 64]. For the MADRS, only two predefined equivalence margins can be found in the literature, both established for medical treatment against placebo and not for CBT as in our study [65, 66] .

Historical trials of cognitive behaviour group therapy have yielded effect sizes of Cohen’s d ranging from 0.4 [67] to 0.68 [68] to 1.3 [35]. The non-inferiority margin can be chosen as half of the mean difference between state-of-the-art therapy and the control treatment [63, 69, 70]. Because it is easier to find non-inferiority if the margin is larger, we will calculate it with the two lower margins of 0.2 (0.5*0.4) and 0.34 (0.5*0.68) from the two current meta-analyses. Therefore, we will calculate Cohen’s d / Hedges’ g of the between-group difference (BPT-CBT).

Furthermore, the difference between CBT and the active control group EP will be calculated, and the mean difference will be used as a supplementary non-inferiority margin as proposed by different authors [63, 69, 70], who suggest controlling for one’s own standard therapy by using an additional control group if historical trials for the estimation of the non-inferiority margin are missing. Because our EP group is designed as an active control group with a therapeutically active intervention (physical activity), the margin found in the comparison between CBT and EP is likely to be conservative compared to an inactive control group. Various authors [63, 69, 71] recommend the definition of the margin based on clinical considerations. At an average severity interval of about 10 points (below 10 points remission, 10 to 20 points mild depression, to 31 points moderate depression [44, 45]), a reduction of at least 5 points appears clinically relevant. The margin to be determined should therefore not exceed 5 points.

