**Methods:**

The study is being conducted as a multicentre randomised controlled intervention trial at three locations in Germany. Participants are being randomised into three groups: BPT, CBT, or EP, each with a 10-week treatment phase. A power analysis indicated that about 240 people should initially be included. The primary outcome of the study is the Montgomery and Asberg Depression Rating Scale (MADRS) directly after the intervention. Additional measurement points are located three, six, and 12 months after the end of the intervention. The data are being collected via computer-assisted telephone interviews. Statistical analyses comprise regression analyses to test for the superiority of BPT over EP. To test for the non-inferiority of BPT and CBT, a non-inferiority margin of 1.9 points in the Patient Health Questionnaire (PHQ-9) and two non-inferiority margins for the MADRS (half of the two smallest Cohen’s d values from the current meta-analyses) was predefined. The mean difference between CBT and EP is being used as a supplementary equivalence margin.

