### Sample size estimation

A power analysis was computed on the basis of the authors’ previous experience with the BPT in the pilot study in which a Cohen’s d of 0.77 was reached [33]. To address Hypothesis I, a slightly lower effect size of 0.6 was assumed. Thus,61 patients will be needed in the BPT group and 61 patients in the EP group (alpha = .05, power = .9).

To address Hypothesis II, a non-inferiority margin of 1.9 points (SD = 3.8) on the PHQ-9 (as proposed in the literature [36]) was used, which resulted in a total of 69 patients in the BPT group and 69 patients in the CBT group (alpha = .05, power = .9). Thus, there should be 61 patients in the EP group, 69 patients in the BPT group, and 69 patients in the CBT group, for a total of 199 patients. To account for dropouts between t0 and t1, 20% more patients are added (based on the drop-out-rate of our pilot study), resulting in 40 additional patients for a total of 239.

Therefore, 10 waves in three therapy centres (two waves in Berlin, four waves in Weyarn, four waves in Erlangen) were planned. Each wave was designed to include 24 participants on average, of which 20 were expected to complete the respective intervention.

Also from the data of the pilot study, in which similar recruitment modalities were applied, a failure of approx. 40% of patients who do not meet the inclusion criteria must be expected. This means that a total of approximately 400 patients should be screened.

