#### Hypothesis I: superiority of BPT over EP

The primary outcome variable is the MADRS. To test the first hypothesis, t-tests for independent groups of change scores (pre-post) will be performed between the BPT and EP groups. In addition, multivariate analyses (ANOVAs and multiple linear regression analyses) will be calculated. To control for the effects of confounders, demographic variables as well as other therapeutic treatments patients used outside of the treatments offered in the study (e.g. antidepressive medication, psychotherapy, offers to participate in additional sports) will be included in the regression analyses.

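### The supplementary MADRS margin (the full observed CBT–EP difference) cancels CBT out of the test whenever that difference is 5 points or less, so the test then mainly repeats BPT versus EP

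*Protocol article*

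**What the plan says.** The section on Hypothesis 2 sets several margins for BPT versus CBT. Three are fixed in advance: 1.9 points on the PHQ-9, and d = 0.2 and d = 0.34 on the MADRS. The two MADRS margins are half of the historical effects 0.4 and 0.68, on the ground that "The non-inferiority margin can be chosen as half of the mean difference between state-of-the-art therapy and the control treatment".

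The next paragraph adds a margin taken from the trial's own data. The CBT–EP difference is calculated, and "the mean difference will be used as a supplementary non-inferiority margin". The abstract repeats this: "The mean difference between CBT and EP is being used as a supplementary equivalence margin". Neither place applies a fraction. The paragraph describes the margin as probably conservative relative to one based on an inactive control, and closes with a clinical limit: "The margin to be determined should therefore not exceed 5 points".

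BPT versus EP is already the subject of Hypothesis I, where "t-tests for independent groups of change scores (pre-post) will be performed between the BPT and EP groups".

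**The concern.** A non-inferiority margin should limit how much of the reference treatment's benefit may be lost. If the margin equals the reference's whole observed advantage over the third arm, a new treatment may lose all of that advantage and still pass. Because the margin comes from the same CBT data as the comparison, a better CBT result raises the bar and widens the margin by the same amount.

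At stake is a supplementary statement of non-inferiority to CBT which, in part of the possible results, carries no information on BPT against CBT.

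**Working it through.** **The plan's own figures.** For Hypothesis I, "a slightly lower effect size of 0.6 was assumed". With two-sided alpha 0.05 and power 0.9, n = 2(1.960 + 1.282)²/0.6² = 58.4, so 59 per arm (60 with the t distribution). The plan's 61 is within 2 of this. For Hypothesis II the plan uses "a non-inferiority margin of 1.9 points (SD = 3.8) on the PHQ-9". With one-sided alpha 0.05, n = 2(1.645 + 1.282)² × (3.8/1.9)² = 68.5, so 69, an exact match. One-sided 0.025 would need 85. The one-sided 5% level used below is therefore the one implied by the plan's 69.

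**The cancellation.** Let B, C and E be the observed mean MADRS reductions in BPT, CBT and EP, and SE the standard error of C − B.

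- Non-inferiority with margin M: (C − B) + z·SE < M.
- Put M = C − E: (C − B) + z·SE < C − E.
- Subtract C from both sides: B − E > z·SE.

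CBT's mean is gone. At the planned sizes (BPT 69, CBT 69, EP 61) the standard error of BPT–CBT is √(2/69) = 0.170 SD and that of BPT–EP is √(1/69 + 1/61) = 0.176 SD, a ratio of 0.969. In simulation at these sizes, without the cap, the decision agreed with a one-sided 5% BPT–EP test in 98.0% to 99.6% of trials. The pass rate depended on the true BPT–EP effect (0.055, 0.545 and 0.965 at 0, 0.3 and 0.6 SD) and not on the true CBT–EP effect.

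**The cap.** If C − E exceeds 5 points, M = 5 and the test again depends on C. The protocol gives no MADRS SD, so I assume 6, 8 or 10, which puts the cap at 0.83, 0.63 or 0.50 SD. At the planned sizes the cap binds in 0.7%, 10% or 28% of trials when the true CBT–EP effect is 0.4 SD, and in 19%, 62% or 85% when it is 0.68 SD. These are the historical effects that the plan halves.

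**Size.** Let BPT truly keep half of the CBT–EP effect, with 64 per arm and z = 1.645. Then SE = √(2/64) = 0.177 SD and z·SE = 0.291 SD.

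- Full difference, no cap: Φ((0.30 − 0.291)/0.177) = 52% at 0.6 SD, and Φ((0.40 − 0.291)/0.177) = 73% at 0.8 SD.
- Fixed d = 0.34: Φ((0.34 − 0.30 − 0.291)/0.177) = 8%, and Φ((0.34 − 0.40 − 0.291)/0.177) = 2%.
- Half the observed difference, still with the SE of BPT–CBT: the quantity tested is B − 0.5C − 0.5E, with true mean 0 and SE √(1.5/64) = 0.153. The rate is 1 − Φ(0.291/0.153) = 3%.
- Capped rates come from simulation.

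| Margin | CBT–EP 0.6 SD | CBT–EP 0.8 SD |
|---|---|---|
| Full difference, capped at 5 points, SD 8 | 38% | 32% |
| Full difference, capped at 5 points, SD 10 | 23% | 13% |
| Full difference, no cap (upper limit) | 52% | 73% |
| Fixed d = 0.34 | 8% | 2% |
| Half the observed difference | 3% | 3% |

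At 69/69/61 the uncapped rates are 55% and 75%.

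**The case against.** - **The margin is supplementary.** This stands. The PHQ-9 margin, which drives the sample size, and both fixed MADRS margins are untouched. A reader might infer that Hypothesis II would be declared supported on the same evidence as Hypothesis I. The protocol does not say that passing this margin alone is enough. The repeat is also not identical: the standard error differs, and the primary analysis set is per protocol for Hypothesis I and intention to treat for Hypothesis II.
- **The cap protects.** In part. A reader might infer that the test never says anything about BPT against CBT. That is true only up to 5 points. Above it CBT counts, and at 0.8 SD the cap removes more than half of the uncapped pass rate for either assumed SD in the table. The capped figures are the plan's rule.
- **The plan calls the margin conservative.** It does so only relative to an inactive control. That comparison is reasonable and is not an error. It does not help here, because below the cap the size of the margin has no effect on the result.
- **The plan breaks its own half rule.** The sentence on halving is permissive and belongs to the preceding paragraph. The contrast is fair, but it is not a breach.
- **The test rule is not spelled out.** Correct: treating the margin as fixed and using a confidence limit is my reading. Allowing for the margin's sampling error would not restore CBT, since (C − B) − (C − E) = E − B whichever standard error is used.
- **Half-retention is not an error under every margin.** Half of 0.6 SD is a deficit of 0.30 SD, inside d = 0.34 though outside d = 0.2. At 0.8 SD the deficit of 0.40 SD lies outside both.
- **The level could be one-sided 2.5%.** The capped rates would then be 26% and 21% (SD 8) or 14% and 7% (SD 10).

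**Conclusion.** The point holds as a fault in a supplementary analysis. Up to an observed CBT–EP difference of 5 points, the cancellation is exact algebra and needs no assumption about the SD. The test then essentially asks the question of Hypothesis I and preserves none of CBT's advantage over EP.

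The pass rates of 38%/32% and 23%/13% rest on 64 per arm, a one-sided 5% level, a BPT that keeps half of the effect, and an assumed MADRS SD of 8 or 10. In the same scenarios this margin is several times more permissive than the looser of the two fixed MADRS margins. The evidence that the fixed margins give on BPT against CBT is not affected.

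**What to change.** Remove the full observed CBT–EP difference as a margin from the section on Hypothesis 2 and from the abstract. Keep the CBT versus EP comparison after treatment as a check that CBT worked in this trial.

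If an internal standard is wanted, test retention of at least half the effect with the contrast B − 0.5C − 0.5E > 0 and its own standard error. At equal n the variance is σ²(1 + 0.25 + 0.25)/n = 1.5σ²/n. This holds its one-sided 5% level at the half-retention boundary and fits the halving already used for the historical margins. State that the result cannot by itself support Hypothesis II in place of the fixed margins.

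The cost is wording and one contrast, with no new data. The downside is that one route to a favourable supplementary statement is lost.

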#### Secondary measurements

Secondary outcome variables such as self-esteem and anxiety will be tested exploratively with t-tests for independent groups.

## Discussion

This is the first study to investigate the effect of a bouldering psychotherapy (BPT) on outpatients’ depressive symptoms compared with evaluated treatment options - namely mere physical activity (superiority analysis) and state-of-the-art cognitive behavioural therapy (CBT, non-inferiority analysis).

The results of the study may contribute to an enlargement of treatment options for outpatients suffering from depression. As bouldering is getting increasingly popular, participation in a bouldering therapy might be more socially accepted and thus may represent a lower threshold-offering than participation in classical psychotherapeutic approaches.

Participants of the study will probably benefit, as they receive additional therapy without incurring additional costs or wait times. All study arms were demonstrated to be effective in the treatment of depression prior to this study. Participants are free to start any additional treatments offered by the German health care system while participating in this study without suffering any disadvantages from study personnel, and patients’ individual ongoing treatment plans are not altered by their participation in this study.

Participants in the BPT group have a slight risk of injuries, but this risk does not exceed the risks of other physical activities. A study on injuries in sport-climbing (which has higher risks of severe injuries than bouldering) with about 2000 climbers revealed an average number of 0.2 injuries per 1000 h of climbing [72]. In our study, participants boulder for a maximum of 10*2 h in total. In our pilot study [33, 34], no SAEs in the BPT occurred in around 2400 bouldering hours. Thus, no serious injuries are expected. Nevertheless, SAEs such as strains, ligament ruptures, or fractures as well as suicidal attempts or actual suicides are documented by the therapists for each group and interim analyses of SAEs will be performed on a regular basis. If any analyses show a cumulation of SAEs in the BPT, being significantly higher than in the CBT and the EP group, the DMSB will be consulted.. If a causal connection with the intervention can be plausibly established, the BPT will be terminated and all patients will be offered CBT instead. In addition, accident insurance is being included in the trial participation for all patients. In case of physical injuries during the BPT sessions, the affected person will be stopped from bouldering and sent to an appropriate specialist for medical clarification. Suicidal thoughts between two sessions should be shortly debriefed with the participant prior to the beginning of the session and a suicidal assessment should be carried out to decide whether the participant can distance him- or herself from suicidal tendencies. In case of a suicidal attempt, the participant will be hospitalized and excluded from the study.

All participants are asked to sign an anti-suicide contract for the duration of the study in the screening questionnaire. Interested persons who are not willing or able to complete the anti-suicide contract are not included in the study but are redirected to other treatment options with higher intensity (e.g. inpatient treatment). During the therapies, all therapists follow good clinical practice in monitoring for suicide risk, and suicide risk management plans in cases of acute risk are established by the study centre.

Strengths of the study design are the randomisation, the three study arms with evaluated treatment options as active control groups and the longitudinal character of the study with a long follow-up period of 1 year after the end of treatment. The use of manualised treatments in a naturalistic setting with recruitment of patients in different regions throughout Germany (with a balanced ratio of urban and rural regions) contributes to a high internal and external validity of the study. In order to be able to replicate and implement the treatment, it is planned to publish the manual of the BPT if results of the study show promise.

As our treatment is a non-drug therapy, it must be given open-label and participants and therapists cannot be blinded. In order to reach high objectivity of the results, CATI interviewers, who assess the outcome data are blinded to group allocation of the participants.

We decided to allow patients to receive additional care and defined only few in- and exclusion criteria. This was due to ethical reasons, as we did not want to disrupt ongoing treatment plans as well as to our approach of a naturalistic design. This however has the disadvantage of clinical heterogeneity of the sample, which may dilute the intervention effects.

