### Study design and setting

To test the research hypotheses, a randomised, controlled, multicentre, prospective longitudinal study with three arms is being conducted. Recruiting for the StudyKuS began in 2017 in three different regions in Germany: a) the Erlangen/Nuremberg/Fuerth region (metropolitan region of three cities), b) the Weyarn region (rural area surrounding Munich), and c) the Berlin (capital) region. Each intervention is being carried out by two therapists (with the exception of the EP, which is supervised by the study’s headquarters) over a period of 10 weeks in groups with a maximum of 11 participants. All of the three interventions in one region are taking place during the same time period and are being conducted in consecutive waves – with four waves in the Erlangen/Nuremberg/Fuerth region as well as the Weyarn region and two waves in the Berlin region. Participants in one region and one wave are randomly allocated to one of the three groups (BPT, CBT or EP). Data are being collected via computer-assisted telephone interviews (CATIs) before and directly after the intervention as well as three, six, and 12 months after the treatment. A data monitoring and safety board (DMSB) is established ([name]) and supervises study conduction and severe adverse events (SAEs). All procedures have been approved by the Friedrich-Alexander-Universität Erlangen-Nürnberg Ethics Committee (Ref. 360_16 B). The participant timeline is presented in Fig. 1. Trial Registration Data are presented in Table 1 (ISRCTN12457760, Registration date: 26 July 2017, registered retrospectively).

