#### Other measures

##### Screening questionnaire

The screening questionnaire is filled out by individuals interested in participating in the study after attending the informational sessions for the purpose of assessing the inclusion and exclusion criteria. It consists of sociodemographic data such as age and gender as well as open questions that reflect the criteria for inclusion and exclusion (e.g. height and weight to calculate BMI, current therapeutic treatment, physical limitations, psychiatric comorbidities, and depressive symptoms as assessed with the PHQ-9).

The following data are being assessed via the CATIs in addition to the questionnaires presented above*:*

*Sociodemographic data* (e.g. family status, level of education).

Data regarding *current occupation* (e.g. ability to work, current sick-leave status).

*Medical history regarding depression* (onset, duration, and progression of depression).

*Current therapeutic treatment* (medical, psychological, and drug treatment as well as inpatient treatment).

*Critical life events* during the past 6 months (e.g. death of a relative).

*Physical activity* (frequency and kind of activity beyond activities included in the study).

*Attitude towards physical activity* (positive or negative attitude).

*Attitude towards future group allocation* (EP, CBT, BPT, comfortable, uncomfortable, no preference)

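### The SAE rule groups strains with suicide attempts under one label, and its only predefined comparison looks for an excess in BPT

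*Protocol article*

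**What the plan says.** The Discussion section of the protocol article puts injuries and suicidal events under one heading: "SAEs such as strains, ligament ruptures, or fractures as well as suicidal attempts or actual suicides are documented by the therapists for each group". It adds that "interim analyses of SAEs will be performed on a regular basis".

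One between-arm rule follows (the sentence closes with consultation of the board): "If any analyses show a cumulation of SAEs in the BPT, being significantly higher than in the CBT and the EP group, the DMSB will". The consequence comes next: "If a causal connection with the intervention can be plausibly established, the BPT will be terminated and all patients will be offered CBT instead".

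Two further provisions are not tied to BPT. Under Study design and setting, the DMSB "supervises study conduction and severe adverse events (SAEs"), with no restriction to one arm. The Discussion also has actions for individuals: suicidal thoughts are to be assessed before a session, and "In case of a suicidal attempt, the participant will be hospitalized and excluded from the study".

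Just before the list of events, the same paragraph cites 0.2 injuries per 1000 h of sport climbing and a pilot study with no SAE in about 2400 bouldering hours. It concludes: "Thus, no serious injuries are expected".

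**The concern.** Injuries and suicidal events behave differently across these arms. Bouldering injuries can arise only in BPT, exercise injuries are possible in EP, and CBT offers little opportunity for either. A causal link between a bouldering strain and bouldering is also easy to accept. Suicidal events can occur in any arm of a depression trial.

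A comparison of SAEs under one label can therefore respond to the less important kind of event and be blunted for the more important kind. It is also one-sided by arm: no comparison is written for an excess in CBT or EP. At stake are the continuation of the experimental arm and the visibility of a suicidality signal. The efficacy hypotheses and their analysis are not affected.

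**Working it through.** **Inputs**
- Arm size: 239 planned in total (Sample size estimation). 239 / 3 ≈ 80 per arm; the equal split is an assumption.
- Significance level 0.05 (Data analysis). Sidedness and test for the SAE comparison are not stated; Fisher's exact test, two-sided, is assumed.
- Bouldering exposure: at most 10 × 2 h = 20 h per participant (Discussion), so 80 × 20 = 1600 h.
- Injury rate: 0.2 per 1000 h (Discussion). Whether it counts strains is not stated.
- All event counts below are assumptions, one event per participant. The plan states no figure for this rule, so there is none to reproduce.

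**1. How many BPT events meet the trigger?**
For k events in BPT and none in a comparator of equal size, two-sided p = 2 × C(80,k) / C(160,k).
- k = 5: p = 0.059.
- k = 6: p = 2 × 0.0142 = 0.028.

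Six events against none in each comparator is therefore the smallest significant excess, and all six could be strains. With the unequal targets inflated by 20% (69 × 1.2 ≈ 83 in BPT, 61 × 1.2 ≈ 73 in EP) it is still six, p = 0.030. One-sided at 80 per arm, five suffice (p = 0.029).

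The rule does not say whether the excess must hold over each comparator or over both combined. Combined, three suffice: C(80,3) / C(240,3) = 492,960 / 13,651,680 = 0.036.

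**2. How likely is that from injuries alone?**
Poisson count with mean rate × 1600 h, at a single look with full exposure and no comparator events:

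| Rate per 1000 h | Expected | P(6 or more) | P(3 or more) |
|---|---|---|---|
| 0.2 (cited) | 0.32 | about 0.000001 | 0.004 |
| 1 (assumed) | 1.6 | 0.006 | 0.22 |
| 2 (assumed) | 3.2 | 0.11 | 0.62 |
| 5 (assumed) | 8.0 | 0.81 | 0.99 |

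The last column applies to the combined reading: 1 − e^(−m)(1 + m + m²/2), with m the expected count. Further looks can only raise the chance of crossing at some look.

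The pilot's zero in 2400 h gives a one-sided 95% upper limit of −ln(0.05) / 2.4 = 1.25 per 1000 h. At that rate 2.0 events are expected and P(6 or more) is 0.017. The limit covers strains only if the pilot counted them as SAEs.

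**3. Can a suicidality excess in BPT be diluted?**
Six attempts in BPT against none in EP: p = 0.028. Add injuries to the EP count:
- one EP injury, 6 vs 1: p = 0.12;
- two EP injuries, 6 vs 2: p = 0.28.

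If the excess must hold over each comparator, the trigger is no longer met. If the comparators are combined, 6 of 80 vs 2 of 160 gives p = 0.018 (the hypergeometric tail, summing C(80,k) × C(160,8−k) / C(240,8) for k = 6 to 8), and the trigger is still met. Dilution thus depends on the first reading.

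**4. The mirror case**
Six attempts in EP against none in BPT also gives p = 0.028, but no written comparison looks in that direction.

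**5. Who records events in EP?**
The Discussion assigns recording to the therapists of each group. Study design and setting says that EP is the exception to delivery by two therapists and is supervised by the study's headquarters. No recorder is named for EP. Under-recording there would make a BPT excess easier to find and an EP excess harder to see.

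**The case against.** **Minor injuries do not end BPT by themselves.** A reader might infer that they do. The text requires a significant excess, then consultation of the DMSB, and a plausible causal connection before termination. This stands; the first step is all that strains can meet on their own.

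**An excess in EP or CBT is not ignored.** A reader might infer that it triggers nothing. The DMSB's remit covers SAEs in the whole study, and individual actions exist for suicidal thoughts and attempts. What is absent is a predefined trial-level comparison. A trigger aimed at the newly developed therapy can also be defended, since the comparators are described as already evaluated.

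**A single sum is partly inferred.** The text does not say that the DMSB would see no breakdown by event type, and an alert board would look at types. This limits the dilution example, but the written trigger is still stated for SAEs as one class.

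**The list of events is open.** It gives examples, so the absence of psychiatric admission is no error, and a condensed article may leave definitions to the full protocol.

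**The counts are invented.** They are illustrations. On the document's own rate a strain-only trigger is remote, and nothing supports a claim that strains would dominate the tally.

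**Expecting no serious injuries may simply be loose wording**, since the following sentence says that events are documented anyway. That is fair, but naming a strain as a severe event leaves unclear what the pilot's zero counted.

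**Conclusion.** The point holds in limited form. The Discussion states an event class that mixes strains with suicidal events and a single comparative trigger directed at BPT. This is a stated rule, so it is not a matter of detail left to another document. As written, a strain-only excess could meet the trigger, with termination possible after the two further steps. A suicidality excess in BPT could be diluted by EP injuries if the excess must hold over each comparator. A suicidality excess in EP or CBT has no predefined trial-level trigger, although general DMSB supervision remains.

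The size depends on assumptions: 80 per arm, a two-sided Fisher test and assumed counts. How often strains would meet the trigger turns on a rate that the documents do not give: negligible at the cited rate, material only if recorded strains are several times more frequent or if the comparators are combined. The change is worth making because it is cheap and concerns the safety comparison, not because a false alarm is likely.

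**What to change.** In the safety paragraph of the Discussion, have the regular interim SAE analyses report injuries and suicidality as separate categories for all three arms, and give the DMSB both comparisons in either direction. State whether an excess means over each comparator or over both combined.

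Reconcile three pairs of statements:
- strains named as severe events, and the expectation of no serious injuries;
- the BPT-only trigger, and the DMSB's study-wide remit;
- recording by the therapists of each group, and an EP arm supervised by headquarters. Name who records SAEs there.

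The telephone interviews ask all arms about current treatment ("medical, psychological, and drug treatment as well as inpatient treatment"). Under Data collection they take place before the intervention, at its end and later. The answers can therefore supplement the table from the end-of-treatment interview onwards, but cannot feed review during a wave. The article also does not say that they identify psychiatric admissions.

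Which events should count towards stopping BPT is for the sponsor and the DMSB. The cost is protocol wording and one more row in the SAE table. The downside is two comparisons instead of one at each review.
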